### Sample size

In the prospective cohort, all patients with CMP who visit the two local networks of NPRL1.0 will be invited to participate in the study. Based on the recruitment results of the feasibility study of NPRL1.0, and the number of patients visiting a GP practice, we expect that each local network will also recruit about six patients per month. Therefore, the two local networks from NPRL1.0 together should recruit approximately 132 patients in 11 months. Assuming a dropout rate of 20%, we expect to include approximately 105 patients in this study.

To calculate the desired sample size for the stepped-wedge based design, we used the method described by Woertman et al. [39]. The calculations of the number of patients needed are based on the primary outcome of the cost-utility analysis, the health-related quality of life measured with the 5-level EQ-5D version (EQ-5D-5L). Based on McClure et al., we consider an increase of 0.063 points (SD = 0.013) in 1 year as clinically relevant [40]. In addition, an alpha of 0.05, a power of 80%, a 1:1 ratio between control and intervention groups, and a dropout rate of 30% were assumed. Based on these values and the stepped-wedge based design, a design effect (DEsw) of 0.416 exists, which leads to a required sample size of 184 patients (92 control and 92 intervention). Based on the recruitment results of the feasibility study of NPRL1.0, and the number of patients visiting a GP practice, we expect that each local network will recruit 6 patients per month [32]. Therefore, with a dropout rate of 30% of local networks, six local networks will need to participate.

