The EQ-5D-5L will be used for the cost-utility analysis: it provides a single health index based on self-reported mobility, self-care, usual activities, pain/discomfort, and anxiety/depression, with a minimal clinically important change of 0.04 [47]. There are five levels in each dimension from which respondents select that which most closely matches their health state. The levels are no, slight, moderate, severe, and extreme problems, coded 1 to 5. A health state index score, ranging from − 0.446 to 1 (worst to best imaginable health status), will be calculated from individual health profiles, using the Dutch utility tariff [48]. QALYs were calculated from utilities by using the area under the curve method. The accompanying visual analogue scale (VAS: 0–100) rates the current health state, with higher scores indicative of better experienced health. The minimal clinically important difference for low back pain is 22.5 [46]. The Dutch version of the EQ-5D-5L was found valid and reliable [49, 50].

The Numeric Rating Scale (NRS) will be used to measure pain intensity on an 11-point scale varying from 0 (no pain) to 10 (worst pain imaginable). At each measurement point (T1-4), the patient will complete the NRS three times: current pain intensity; lowest pain intensity in the last week; highest pain intensity in the last week. The NRS has shown high test–retest reliability and validity [51]. A reduction of 2 points, or 30%, on the pain NRS scores can be seen as clinically important [52].

The Hospital Anxiety and Depression Scale (HADS) consists of 14 items of which seven are related to anxiety and seven to depression. The patient is asked to rate the items on a 4-point scale ranging from 0 (not at all) to 3 (most of the time). Total scores range from 0 to 21 on each subscale: a higher score reflects higher distress. The HADS has a sensitivity and specificity of about 80% and a predictive validity for identification of about 70% [53]. The reliability ranges from 0.84 to 0.96 [54].

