### Data analysis

Demographic data (e.g. gender, age, home situation, level of education, nationality, and co-morbidities) will be described overall and separately for the intervention and control groups. Frequencies are to be presented for categorical variables, means and standard deviations (SDs) for normally-distributed continuous variables, and medians and ranges for non-normally-distributed continuous data. The two groups will be tested on differences between characteristics, using the *t*-test for continuous variables and the chi-squared test for categorical variables. If variables differ between the two groups, with *p* ≤ 0.10, they are considered to be potential confounders in further analyses.

Outcomes on questionnaires will be compared using linear mixed-model analysis, to take into account repeated measurements in patients as well as the effects of the clustering of patients within local networks. The fixed part of the model contains treatment group (intervention/control), time, treatment group*time, and cluster (local network). To assess the learning effect in local practices, the time (months) that a local network participates in NPRL2.0 will also be taken into account as a fixed variable. Variables known to be related to the outcome and differing between treatment groups at T1 (*p* ≤ 0.10) will be added to the model. An unstructured covariance structure will be used for repeated measures. Missing values for items in the questionnaires will be handled according to the scoring algorithms of the questionnaires. Missing variables in the follow-up data will not be imputed because linear mixed-model analysis is a flexible method for handling missing data for stepped-wedge and repeated-measures designs (likelihood-based approach). Linear mixed-model analyses will be performed using IBM SPSS Statistics for Windows (version 24.0 or higher, Armonk, NY: IBM Corp.) according to the intention-to-treat principle. Other missing values for non-repeated measures will be handled by multiple imputation, which means that missing values will be predicted using existing values for other variables [66].

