Costs will be compared using bootstraps (1000 replications) with Microsoft Excel 2016 with mean differences and 95% confidence intervals. Subsequently, sample uncertainties around the incremental cost-effectiveness ratio (ICER) and incremental cost-utility ratio (ICUR) will be explored using bootstrapping with a minimum of 5,000 replications. The ICER and ICUR will be defined by the difference in costs between NPRL2.0 and the control group, divided by the difference in incremental effects of the SF-12 and incremental QALYs respectively. Cost-effectiveness analyses will be performed with the mean total costs and the mean SF-12 scores. The cost-utility analysis will be performed by relating the mean total costs to the mean QALY scores of both groups, and the bootstrapped ICURs will be plotted in cost-effectiveness planes. Moreover, uncertainties of the ICERs and ICURs will be graphically presented in cost-effectiveness planes (CE plane), as well as cost-effectiveness acceptability curves (CEAC). A CEAC will be calculated to describe the probability of NPRL2.0 being a cost-effective alternative to the control group [67]. This CEAC includes the amount of money the society is willing to pay (WTP) in order to gain one unit of effect (one QALY here). The WTP threshold in the Netherlands for one QALY is based on the health burden and varies between €20,000 (health burden 0.1 to 0.4), €50,000 (health burden 0.41 to 0.7) and €80,000 (health burden 0.71 to 1) (2015) [68].

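### The economic evaluation is fixed as a bootstrap of group means with no baseline-utility or network adjustment, and the reason given for not imputing follow-up data does not cover its costs and QALYs

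*Protocol article*

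**What the plan says.** **Effect analysis (Data analysis).** Questionnaire outcomes go into a linear mixed model. Its fixed terms are arm, follow-up time, their interaction, local network, months of participation, and covariates that differ at T1.

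**Economic analysis (Data analysis).** This is laid out separately. For costs: "Costs will be compared using bootstraps (1000 replications) with Microsoft Excel 2016", giving mean differences and 95% intervals. For cost-utility: "The cost-utility analysis will be performed by relating the mean total costs to the mean QALY scores of both groups". Cost-effectiveness is treated the same way with mean SF-12 scores. The ICER, ICUR, planes and acceptability curve all follow from these means. No T1-utility covariate, network term or resampling within networks is named. None of the four sensitivity analyses adds one or concerns missing data.

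**QALY construction (Health assessment).** "QALYs were calculated from utilities by using the area under the curve method". According to the Abstract, the EQ-5D-5L and both iMTA questionnaires are completed at T1, T2, T3 and T4.

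**Missing data (Data analysis).** "Missing variables in the follow-up data will not be imputed because linear mixed-model analysis is a flexible method for handling missing data". Multiple imputation is kept for other missing values of non-repeated measures.

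**The concern.** Three protections given to the effect analysis are not carried into the economic one.

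- **Baseline utility.** T1 utility is one of the four points under the QALY curve. Patients are recruited before or after the network's transition and are not individually randomised. The Discussion only expects the two groups to be comparable. A T1 difference therefore passes into the QALY difference, directly and through its correlation with later utilities.
- **Network.** The Study design section justifies the stepped wedge by its control of between-network variation, and the Discussion says networks serve as their own controls. A difference of pooled means does neither when networks contribute unequally to the arms.
- **Missing data.** Likelihood handling of incomplete follow-up belongs to the mixed model. A bootstrap of total costs and QALYs has no such property, so the reason for not imputing does not reach these outcomes.

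Aims 2 and 3 rest on this analysis. An adjusted EQ-5D-5L result and an unadjusted QALY result from the same patients could point different ways, and the article does not say which would prevail.

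**Working it through.** **1. Which SD to use.** The plan states: "we consider an increase of 0.063 points (SD = 0.013) in 1 year as clinically relevant". It also states: "an alpha of 0.05, a power of 80%, a 1:1 ratio between control and intervention groups, and a dropout rate of 30% were assumed". With SD 0.013 the standardised effect is 0.063/0.013 = 4.85, and 1 to 3 patients per arm would be enough. The stated 184 does not follow from that, so the printed SD cannot be used here. Two SDs lead back to about 184, and I take them as an assumed range:

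- SD 0.126 (standardised effect 0.5, no design effect): the t-test needs 64 per arm; 64/0.7 = 91.4, so 92; 2 × 92 = 184.
- SD 0.198 (design effect 0.416 and 30% dropout applied): 184 × 0.7/0.416/2 = 154.8 per arm; SD = 0.063/[(1.960 + 0.842) × √(2/154.8)] = 0.198.

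The sample-size mismatch is a separate matter, and this point does not depend on it.

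**2. Network mix.** Inclusion months are 3 control and 5 intervention for A, 4 and 4 for B, 5 and 3 for C, so 12 in each arm. With equal monthly recruitment per network (the plan expects six patients per month), the raw difference carries (5/12 − 3/12)A + (4/12 − 4/12)B + (3/12 − 5/12)C = (A − C)/6. An A-minus-C utility difference of 0.03 to 0.10 (assumed) would add 0.005 to 0.017 to the raw utility contrast.

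**3. Missing data.** 92 × 0.7 = 64.4, so about 64 per arm would have complete data if nothing is imputed.

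**4. Baseline utility in the QALY.** Trapezoid weights over 0.75 year are 0.125 (T1), 0.25 (T2), 0.25 (T3) and 0.125 (T4). If a T1 imbalance u carries forward with correlation r (equal SDs at all waves assumed), the QALY difference moves by u × (0.125 + 0.625r). At r = 0.6 the multiplier is 0.50.

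A gain of 0.063 present in full at T2, T3 and T4 is worth 0.063 × 0.625 = 0.0394 QALY.

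| Assumed SD | SE of T1 difference, SD × √(2/64) | Shift for 1 SE, r = 0.6 | Share of 0.0394 |
|---|---|---|---|
| 0.126 | 0.0223 | 0.0111 | 28% |
| 0.198 | 0.0350 | 0.0175 | 44% |

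For r from 0.5 to 0.7 the multiplier is 0.4375 to 0.5625. The shift is then 0.010 to 0.013 (SD 0.126) or 0.015 to 0.020 (SD 0.198).

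If 0.063 is instead reached linearly at 9 months, the target is 0.063 × 0.75/2 = 0.0236 QALY, and the shares rise to 47% and 74%.

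At EUR 20,000 per QALY the 1-SE shift is worth about EUR 223 to 350 per patient. At EUR 80,000 it is worth about EUR 891 to 1,400.

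**The case against.** **The lack of adjustment is read from silence in a condensed article.** The text never says raw or unadjusted, and the rule that characteristics differing at p ≤ 0.10 are potential confounders in later analyses could be read to reach the economic part. This carries some weight. But the article fixes the economic method closely (estimator, software, replications, four sensitivity analyses), and the operative step of the confounder rule is to add variables to the mixed model. Even if the rule did apply, a 1-SE imbalance (p about 0.32) would not trigger it.

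**A reader might infer that the plan defines a complete-case set. It does not.** Recruitment of patients states intention-to-treat. A per-patient QALY or total cost is a single value and could be read as a non-repeated measure open to multiple imputation. Consultation and treatment hours come from patient records, so that cost component survives questionnaire dropout. What stands is that the utilities and iMTA questionnaires are repeated follow-up measures. Read naturally, the rule leaves them unimputed, for a reason that does not apply to them.

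**A reader might infer that the trial is powered on this unadjusted comparison.** The Sample size section says "The calculations of the number of patients needed are based on the primary outcome of the cost-utility analysis", but the effect it uses is an EQ-5D-5L score change. As a questionnaire outcome, that score is also covered by the mixed model. No QALY or ICUR difference was powered.

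**Chance imbalance is not bias, and the steps are randomly allocated.** Both are right. A bootstrap interval already reflects chance imbalance between patients, and no systematic A-minus-C difference is expected in advance. Baseline and network adjustment would nevertheless remove variation that the plan leaves in.

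**Conclusion.** The point holds in this form. The economic contrast is fixed as a bootstrap of group means with no adjustment for T1 utility or network, and the handling of missing T2-T4 costs and utilities is left without a valid basis.

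The 1/6 network weight follows from the schedule under equal monthly recruitment. The shift of about 0.011 to 0.0175 QALY (28% to 44% of 0.039) rests on an assumed SD, an assumed correlation of 0.6, 64 patients per arm and a gain sustained from T2. It measures avoidable imprecision. It should not be read as an estimate of bias; bias would arise only if patients recruited before and after the transition differ systematically, which the documents neither show nor rule out.

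The remedy should not include a calendar-time term. The mixed model has none: its time terms are follow-up time and months of participation. With a common start (assumed, as the design figure is not shown), control recruitment falls in months 1-5 and intervention recruitment in months 7-11. No month contains both arms, so calendar period could not be separated from arm without extrapolation.

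**What to change.** In Data analysis:

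1. State that the no-imputation rule applies only to outcomes analysed by the mixed model.
2. For the economic evaluation, multiply impute missing T2-T4 EQ-5D-5L and cost data by arm.
3. Estimate incremental QALYs by regression on arm, network and T1 utility, and incremental costs by regression on arm, network and T1 cost.
4. Bootstrap patients within network-by-arm.
5. Use these adjusted increments for the ICER, ICUR, cost-effectiveness planes and acceptability curves.
6. Keep the unadjusted comparison of means as a sensitivity analysis.

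The cost is some extra analysis work and statistical software instead of Excel. No new data are needed, since T1 utility, T1 cost and network are already collected.

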**Methods:**

In this pragmatic study, it is expected that two local networks with 105 patients will participate in the prospective cohort study and six local networks with 184 patients in the stepped-wedge based design. Healthcare professionals in the local networks will recruit patients. Inclusion criteria: age ≥ 18 years; having CMP; willing to improve functioning despite pain; and adequate Dutch literacy. Exclusion criteria: pregnancy; and having a treatable medical or psychiatric disease. Patients will complete questionnaires at baseline (T1), 3 months (T2), 6 months (T3), and 9 months (T4). Questionnaires at T1 and T4 will include the Pain Disability Index and Short Form Health Survey. Questionnaires at T1, T2, T3, and T4 will include the EQ-5D-5L, and iMTA Medical Consumption and Productivity Cost Questionnaires. Outcomes will be compared using linear mixed-model analysis and costs will be compared using bootstrapping methods.

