**Fig. 3 Fig3:**
[figure not shown]
Content of data collection in ‘Patients in cohort’: patients participating in the prospective cohort design; ‘Patients in stepped-wedge based control period: data collection for patients participating in the control group of the stepped-wedge based design; ‘Patients in stepped-wedge NPRL2.0; data collection for patients participating in the intervention group of the stepped-wedge design

Patients participating in NPRL2.0 are asked to fill in four questionnaires electronically or on paper: T1 after initial contact with healthcare professionals about their CMP complaints (50 min completion time); T2 3 months after T1 (30 min completion time); T3 6 months after T1 (30 min completion time); and T4 9 months after T1 (50 min completion time).

Additionally, assessment tool 1 will be used for research purposes, as well as for decision-making in primary care. Therefore, patients in the control group will complete assessment tool 1 as part of the questionnaire at T1. Patients in the intervention group will complete it during their consultations in primary care. Assessment tool 1 will assess the level of complexity of the pain complaints and consists of one Visual Analogue Scale (VAS) for pain intensity and nine dichotomous questions on biopsychosocial factors.

At the end of the study, records of the treatment characteristics of each patient will be collected from the participating practices and rehabilitation centers.

In order to encourage completion of the questionnaires, patients will be reminded up to three times by phone if they have not responded within one week. If incomplete questionnaires are returned, patients will be contacted by phone to answer the remaining questions. The researcher who performs the analyses will be blinded as to patient allocation.

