Four sets of sensitivity analyses will be performed to measure the robustness of the economic evaluation. These analyses will explore the impact of an assumption on the results when changing one value of one parameter while keeping all the other parameter values unchanged [69]. One sensitivity analysis will be performed to measure the influence of taking the educational costs included the intervention costs. Because healthcare professionals will only need training once, the intervention costs may be overestimated. The secondary sensitivity analysis will be performed to assess the influence of the multidisciplinary consultation costs. No standard cost price exists for multidisciplinary consultations in primary care in the Netherlands and it is not known how many patients will be discussed in order to be able to split the costs over these patients. The tertiary sensitivity analysis will be performed to see if there is over- or under-reporting of healthcare consumption in the iMCQ. The data from the records regarding GP and therapist sessions will be compared with the patient data from the iMCQ. When over- or under-reporting is found, a secondary cost analysis will be performed with corrections on all healthcare consumption data, assuming that the same amount of over- or under-reporting is present in the iMCQ. In a fourth sensitivity analysis the impact of the SF-6D to calculate QALYs instead of the EQ-5D-5L will be assessed.

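### The SF-6D sensitivity analysis changes the number of measurement waves as well as the utility instrument, so it cannot isolate the effect of the instrument

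*Protocol article*

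**What the plan says.** **Schedule (protocol article, Abstract, Methods).** For the short-form survey: "Questionnaires at T1 and T4 will include the Pain Disability Index and Short Form Health Survey". For the utility and cost instruments: "Questionnaires at T1, T2, T3, and T4 will include the EQ-5D-5L, and iMTA Medical Consumption and Productivity Cost Questionnaires". The waves fall at 0, 3, 6 and 9 months. The Data collection section fits a shorter middle set: "T2 3 months after T1 (30 min completion time); T3 6 months after T1 (30 min completion time); and T4 9 months after T1", with 50 minutes given for both T1 and T4.

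**Instruments (Health assessment).** The SF-12 is the only short-form survey listed, and the SF-6D is introduced alongside it for use in a sensitivity analysis. On the QALY method: "QALYs were calculated from utilities by using the area under the curve method".

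**Sensitivity analyses (Data analysis).** Four sets are planned. The general rule is stated as "changing one value of one parameter while keeping all the other parameter values unchanged". In the fourth, "the impact of the SF-6D to calculate QALYs instead of the EQ-5D-5L will be assessed". The text mentions neither the different number of waves nor an EQ-5D-5L comparison restricted to T1 and T4.

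**The concern.** The purpose of the fourth analysis is to learn whether the cost-utility result depends on the choice of utility instrument. On the stated schedule the base-case QALY is a four-point area under the curve, while the SF-6D QALY is a straight line from baseline to 9 months. Two things change at once, although the paragraph's own rule allows one.

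A different ICUR could then come from the instrument, from the missing 3- and 6-month utilities, or from both. The two effects could also offset each other and give a reassuring agreement that says little about the instrument. The SF-6D has no 3- or 6-month values with which to tell these cases apart. What is at stake is the robustness statement attached to an ICUR that will be read against willingness-to-pay thresholds of €20,000, €50,000 or €80,000 per QALY.

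**Working it through.** The plan gives no QALY figure for this analysis, so there is nothing to reproduce. The check asks how far the schedule alone can move the incremental QALY when the instrument and the true utilities stay the same.

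**Inputs from the protocol article**
- Waves at 0, 0.25, 0.50 and 0.75 years (Abstract).
- EQ-5D-5L at all four waves; Short Form survey at T1 and T4 (Abstract).
- QALYs by area under the curve (Health assessment), taken here as the trapezoid rule.
- A utility difference of 0.063 (Sample size), used only to give a sense of scale.

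**Assumed, because the documents give no trajectories**
- The shape of the between-group utility difference over time, d1 to d4, with d1 = 0 in the examples.
- The same incremental cost in both runs.

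**Formulas**
- Four waves: 0.125·d1 + 0.25·d2 + 0.25·d3 + 0.125·d4
- Two waves: 0.375·d1 + 0.375·d4
- Two-wave minus four-wave: 0.25·(d1 + d4 − d2 − d3)

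The two agree when d2 + d3 = d1 + d4.

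**Results, as multiples of a gain g**

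| Assumed profile (T1, T2, T3, T4) | Four waves | Two waves | Change in QALY gain | ICUR multiplier |
|---|---|---|---|---|
| Linear (0, 1/3, 2/3, 1) | 0.375g | 0.375g | 0% | 1.00 |
| From 6 months, held (0, 0, 1, 1) | 0.375g | 0.375g | 0% | 1.00 |
| By 3 months, held (0, 1, 1, 1) | 0.625g | 0.375g | −40% | 1.67 |
| Only at 9 months (0, 0, 0, 1) | 0.125g | 0.375g | +200% | 0.33 |
| Early peak, fading to half (0, 1, 0.75, 0.5) | 0.500g | 0.1875g | −62.5% | 2.67 |
| Early, gone by 9 months (0, 1, 0.5, 0) | 0.375g | 0 | −100% | undefined |

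**On the utility scale with g = 0.063**
- By 3 months and held: 0.625 × 0.063 = 0.0394 QALY against 0.375 × 0.063 = 0.0236.
- Only at 9 months: 0.125 × 0.063 = 0.0079 against 0.0236.

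The percentages do not depend on g.

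**Baseline.** Before any adjustment, the weight on a T1 difference rises from 0.125 to 0.375, a factor of three. The Data analysis section itself allows for groups that differ at T1.

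**The case against.** Several objections have force.

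- **The schedule need not matter.** If the between-group difference grows linearly, or more generally if d2 + d3 = d1 + d4, two and four waves give the same answer. This stands. A reader might infer that the analysis can show nothing about the instrument, but the arithmetic does not support that. The effect of the instrument may come through undistorted; the planned SF-6D data alone cannot show whether it did.
- **The schedule evidence is limited.** The wave-by-wave content appears in text only in the abstract, which says what the T1 and T4 questionnaires include and does not say that the Short Form survey is absent at T2 and T3. Fig. 3, which sets out the content, is not shown. That the SF-6D comes from the SF-12 is an inference. These limits stand. However, the abstract lists the two groups of instruments separately by wave, the completion times fit, no other short-form survey is named, and nothing in the text points the other way.
- **The comparator is not spelled out.** The article gives this analysis one sentence, and a fuller document might contain a matched T1/T4 run. That is possible. Even so, the article states the schedule, the one-parameter rule and the swap, and taken together as written they conflict.
- **The rule is a general introduction, and fewer waves merely follow from the available data.** This explains the second change but does not remove its effect on the result.
- **The larger figures come from chosen profiles.** They do. They illustrate a range that includes no effect and do not predict what the trial will find.

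**Conclusion.** The point holds in a bounded form. On the schedule given in the abstract, the fourth sensitivity analysis changes both the instrument and the number of waves, contrary to the rule stated in the same paragraph, and so cannot isolate the contribution of the instrument. The distortion ranges from none (linear change) to a 40% fall or a threefold rise in the incremental QALY for a gain that is early and held or appears only at 9 months. It is larger still if an early gain fades.

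This rests on the abstract's schedule being complete, on the SF-6D being derived from the SF-12, on trapezoid areas, and on assumed trajectories with an unchanged cost difference.

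A reader might go further and infer that the cost-utility result itself is in doubt. The documents do not support that: the base-case EQ-5D-5L QALY, its ICUR and the planned acceptability curve do not use the SF-6D. The consequence is confined to one robustness claim. The change is still worth making, because it alters what that claim can say and costs almost nothing.

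**What to change.** Add one reference calculation to the fourth sensitivity analysis: an EQ-5D-5L QALY computed from T1 and T4 only, preferably in the same patients as the SF-6D QALY. Then report two contrasts.

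1. Four-wave against two-wave EQ-5D-5L shows the effect of the schedule. In the assumed early, sustained case with a gain of 0.063, this is the step from 0.0394 to 0.0236 QALY.
2. Two-wave EQ-5D-5L against two-wave SF-6D shows the effect of the instrument, with the schedule held fixed as the protocol's own rule requires.

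The text should also state at which waves the SF-6D is available.

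The cost is one extra calculation on data already planned, with no added burden on patients. The limitation is that the instrument comparison covers T1 and T4 only and says nothing about agreement at 3 and 6 months.
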